### Participants

Adults (≥18 years) attending for an eye examination at the participating community optometry practices who undergo an OCT scan will be considered for participation in the study. Only people with a suspicion of retinal disease in the opinion of the community optometrist will be recruited in the RCT and diagnostic accuracy study. As entire optometry practices (clusters) will be randomised into standard care or teleophthalmology, patients who are approached and agree to take part in the study will consent (online supplemental appendix 2) to data collection and analysis—there will not be patient-level randomisation. The patient-level inclusion criteria are outlined in box 1.

Box 1Patient-level selection criteria
**Inclusion criteria**
Able to give consent and understand the study.Able to cooperate by following study-specific instructions.Adults (≥18 years) attending the involved community optometry practices who underwent an optical coherence tomography (OCT) scan.Individuals who at the opinion of the community optometrist have any suspicion of a retinal condition (including atrophic (‘dry’) age-related Macular Degeneration (AMD), wet AMD, diabetic retinopathy, macular oedema, macular holes, epiretinal membranes, central serous chorioretinopathy, genetic eye disease).Macular OCT scan performed at community optometry.
**Exclusion criteria**
Individuals with any non-retinal ocular comorbidities in either eye other than cataract.Individuals with media opacities, inability to position or fixate or any other reason that prevents acquisition of good-quality OCT scans (at the discretion of the community optometrist).

### Allocation to trial groups

Simple randomisation will be performed for involved optometry practices into the intervention and control arms. Randomisation will be performed with the unit of allocation being the cluster rather than the individual and allocation concealment will be at the cluster level. Optometry practices will be randomised 1:1 to standard care or teleophthalmology stratified by the hospital site. Optometry practices are committed to the allocated study arm for the duration of the recruitment period or until they have recruited the minimum of the per cluster recruitment range (10 patients).

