### Setting

For the C-RCT and diagnostic accuracy study, patients will be recruited at 24 optometry practices (clusters) in the catchment areas of four HES sites: Moorfields Eye Hospital NHS Foundation Trust (8–10 practices), Birmingham University Hospitals NHS Foundation Trust (4–6 practices), Central Middlesex Hospital at London North West University Healthcare NHS Trust (4–6 practices) and North West Anglia NHS Foundation Trust (4–6 practices). Twelve clusters (each cluster is an optometry practice) will be randomised to standard care and 12 clusters to the intervention (teleophthalmology). This selection of sites includes urban, suburban and rural locations within the UK allowing the inferences made from this study to be applicable to more of the UK population. Two additional optometry practices (clusters) will be randomised (1:1) in a reserve capacity in case of a cluster drop-out or in order to accelerate the recruitment process (online supplemental appendix 1)

10.1136/bmjopen-2021-055845.supp1Supplementary data

For the pragmatic, observational, postimplementation substudy, patients will be recruited at 12 optometry practices (clusters) in the catchment area of Manchester University NHS Foundation Trust. These practices have adopted a teleophthalmology referral pathway as standard practices.

The enrolment start date is September 2020 with anticipated primary completion date in August 2023. Eligible practices need to have OCT devices and the activity volume and track record of referral to HES that will allow achieving the per practice recruitment target.

All OCT scans and clinical vignettes from each case will be transferred to the Moorfields Reading Centre that will provide the reference standard (diagnosis and referral recommendation). All suitable OCT scans will be processed by the DeepMind algorithm at the Moorfields Reading Centre in ‘real-time’ for the AI diagnostic accuracy study.

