## Data analysis plan

### Statistical analysis

In the superiority C-RCT of teleophthalmology pathway study, the primary analysis will be conducted following an intention-to-treat principle, where all randomised patients are analysed in their allocated group whether or not they receive their randomised management plan. The primary outcome is the proportion of false referrals, measured at the patient level. This will be compared between management groups using logistic regression adjusting for clustered centres. Outcomes will be reported as adjusted ORs.

In the AI diagnostic accuracy study, we will report estimates of sensitivity and specificity of the DeepMind algorithm for referral decisions with 95% CIs. Our primary analysis will combine urgent and standard referral to HES and compare against no referral to HES, but a sensitivity analysis will be conducted to evaluate urgent referrals. The full statistical consideration and analysis is provided in online supplemental appendix 4.

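### The allocation section names simple randomisation, which does not deliver the site-stratified 1:1 allocation or the 12 practices per arm stated elsewhere; the primary model's 'centres' also needs defining

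*Protocol article*

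**What the plan says.** Under Allocation to trial groups, the Protocol article opens with "Simple randomisation will be performed for involved optometry practices into the intervention and control arms". It then identifies the practice as the unit ("Randomisation will be performed with the unit of allocation being the cluster rather than the individual") and goes on: "Optometry practices will be randomised 1:1 to standard care or teleophthalmology stratified by the hospital site".

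The Setting section gives the numbers. It states that "patients will be recruited at 24 optometry practices (clusters) in the catchment areas of four HES sites" and that "Twelve clusters (each cluster is an optometry practice) will be randomised to standard care and 12 clusters to the intervention (teleophthalmology"). The largest hospital is to supply 8 to 10 practices and each of the other three 4 to 6. It adds a reserve: "Two additional optometry practices (clusters) will be randomised (1:1) in a reserve capacity".

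For the primary outcome, the Statistical analysis section says: "This will be compared between management groups using logistic regression adjusting for clustered centres". It does not define 'centres', and it refers to supplemental appendix 4 for the full analysis. That appendix is not among the documents at hand.

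**The concern.** Simple randomisation means unrestricted randomisation: each practice is assigned independently, with probability one half for each arm. A 1:1 ratio is compatible with that if it is only the probability of each arm. A fixed 12 per arm is not. Nor is stratification in any useful sense, because independent draws made hospital by hospital have the same distribution as independent draws made from one list. Stratification works only through restriction within the strata, such as blocks or a constrained list.

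With 24 units and three strata of only 4 to 6 practices, the difference is practical. If the named method were followed literally, one hospital could have practices in a single arm. Arm and hospital would then be confounded at that site, and it would contribute nothing to a within-hospital comparison. Hospital is not a neutral label here: in the intervention arm, clinicians at the corresponding hospital make the remote referral decision.

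The analysis sentence adds a second uncertainty. If 'centres' means hospitals, the sentence does not say how correlation within practices is handled. If it means practices, the sentence does not say whether the stratification factor is in the model.

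**Working it through.** **Inputs, all from the Protocol article.** 24 practices, 12 per arm, four hospitals, one with 8 to 10 practices and three with 4 to 6 each, and two reserve practices (Setting). Simple randomisation, 1:1, stratified by hospital (Allocation to trial groups).

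**The plan's own figure.** 12 per arm agrees with 24 × 1/2. The question is how often the named method produces it.

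**Overall split under simple randomisation.** The number of practices in one arm is binomial with n = 24 and p = 0.5.

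- P(exactly 12:12) = C(24,12)/2^24 = 2,704,156/16,777,216 = 0.161
- P(14:10 or worse) = 2 × P(X ≥ 14) = 0.541
- P(15:9 or worse) = 2 × P(X ≥ 15) = 0.307
- P(16:8 or worse) = 2 × P(X ≥ 16) = 0.152

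**Split within hospitals.** A hospital with n practices is one-armed with probability 2 × 0.5^n, which is 12.5%, 6.3% and 3.1% for n = 4, 5 and 6. The chance that at least one hospital is one-armed is 1 − Π(1 − 2 × 0.5^n) over the four hospitals. The chance that a hospital is balanced to within one practice is C(n, n/2)/2^n for even n, and twice C(n, (n−1)/2)/2^n for odd n; the product over hospitals gives the third column. All site-size combinations within the stated ranges that sum to 24 are listed.

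| Site sizes | At least one hospital one-armed | Every hospital balanced to within one |
|---|---|---|
| 8, 4, 6, 6 | 18.5% | 1.0% |
| 8, 5, 5, 6 | 15.5% | 3.3% |
| 9, 4, 5, 6 | 20.8% | 3.6% |
| 9, 5, 5, 5 | 17.9% | 12.0% |
| 10, 4, 4, 6 | 26.0% | 1.1% |
| 10, 4, 5, 5 | 23.3% | 3.6% |

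Worked example for 10, 4, 4, 6: 1 − (1 − 2/1024)(1 − 2/16)²(1 − 2/64) = 1 − 0.998 × 0.7656 × 0.96875 = 0.260.

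**Reserve pair.** Under independent draws both reserve practices fall in the same arm with probability 2 × 0.5² = 50%.

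**Does stratified blocking alone secure 12:12?** Only sometimes. With blocks of two inside each hospital:

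- All four sizes even (8/4/6/6 or 10/4/4/6): 12:12 with certainty.
- Two odd sizes: each leaves one unpaired practice, so P(12:12) = 2/4 = 50% and the worst case is 13:11.
- Four odd sizes (9/5/5/5): P(12:12) = C(4,2)/2^4 = 6/16 = 37.5% and the worst case is 14:10.

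Deleting the word 'simple' is therefore not enough. The scheme has to be named, because the stated 12:12 may need a constraint across hospitals as well as within them.

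**The case against.** The strongest reply is that 'simple' is loose wording. Stratification by hospital, 12 per arm and a 1:1 reserve pair all point to restricted allocation, and one word points the other way. On that view the probabilities above show that the word is wrong, not that the trial will be unbalanced. This stands as far as it goes: the figures describe the method named and do not predict the actual allocation. It does not remove the contradiction. The text would still have to name the restricted scheme, and stratification alone does not guarantee 12:12.

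A related reply is that 'simple' could mean drawing 12 of the 24 practices by lot. That would deliver 12:12 but not balance by hospital, so the conflict with stratification would remain.

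It can also be said that block sizes and list construction belong in a full protocol. That is fair, and their absence is not the point. The point is that statements made in the article disagree with each other.

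A reader might further infer that the primary model omits the hospital strata, and that its confidence interval will therefore be too wide. The article does not support this. 'Clustered centres' may mean practices, hospitals, or both, and the full analysis is in an appendix that is not shown. Any figure for the loss of precision would also need an intracluster correlation and a between-hospital share of it, and the article gives neither. What stands is that the term is ambiguous.

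**Conclusion.** The contradiction is real and can be read directly from the text. Taken at its word, simple randomisation of 24 practices gives the stated 12:12 in 16% of allocations and 15:9 or worse in 31%. It leaves at least one hospital one-armed in about 15% to 26%, depending on how the 24 practices divide among the four sites. These probabilities assume only independent assignment with probability one half and the site ranges in the Setting section.

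The article gives enrolment as starting in September 2020, so practices may already be allocated, possibly by a sound restricted method. The text does not allow a reader to tell. The point calls for a correction of the description and, only if allocation is still open, of the method. It does not show that the trial is biased.

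On the analysis, the conclusion is limited to ambiguity: the sentence on the primary model does not make clear whether it addresses the unit of randomisation, the stratification factor, or both.

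**What to change.** **Allocation.** Replace 'simple randomisation' with one restricted method stratified by hospital site. One that meets every stated condition is a random draw from the set of allocation lists with 12:12 overall and an arm difference of at most one in each hospital. Such lists exist for every site-size combination above, because a total of 24 forces an even number of odd-sized hospitals. Reserve practices should be allocated in a way that respects their own hospital's stratum. The article does not say that the two share a site, so treating them as a single block could disturb the balance within hospitals. If practices are already allocated, state the method actually used and the resulting split by hospital and arm.

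**Analysis.** Define 'centres'. State that the primary logistic model accounts for clustering by practice and includes hospital site as a fixed effect (four sites, so 3 degrees of freedom). If supplemental appendix 4 already says this, align the article's sentence with it.

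**Cost.** A change of wording, a constrained list if allocation is still open, and at most one model term. If site is added, the reported odds ratio is conditional on hospital, and the text should say so.

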### Superiority C-RCT of teleophthalmology pathway

Community optometry practices will be randomised to either continue with standard care for referral of retinal disease to hospital-based eye clinics or move to the teleophthalmology digital referral pathway (figure 1).

**Figure 1 F1:**
[figure not shown]
Superiority cluster randomised trial arms. HCI, human–computer interaction; OCT, optical coherence tomography.

### Intervention arm for superiority C-RCT: digital pathway

The intervention pathway is the teleophthalmology model for referral of patients with suspicion of retinal disease from community optometry to HES using a digital referral platform. Patients who attend at participating community optometry practices will undergo a clinical assessment and OCT scan.

Participants’ OCT scan and clinical information will be transferred via the digital referral platform to corresponding HES. In each case, human expert clinicians based in HES (ophthalmologists or specialist optometrists with a minimum of 2 years experience of independent practice in the context of HES retinal clinics) will make a referral decision remotely (‘tele-HES’) after review of OCT scan and clinical information on the digital referral platform. A referral recommendation by the community optometrist will also be recorded but not acted on, to measure the proportion of correct/incorrect referrals in each arm (online supplemental appendix 3).

The remote review of OCT scans and clinical data at ‘tele-HES’ will be performed by expert clinicians (medics or specialist optometrists) experienced in retinal clinics (minimum of 2 years experience of independent practice in the context of retinal clinics in HES) based at Moorfields Eye Hospital, Central Middlesex Hospital, North West Anglia NHS Foundation Trust Hospitals or Queen Elizabeth Hospital Birmingham with access to senior advice by Consultant Ophthalmologists specialising in retinal disease.

### Control arm for superiority C-RCT: standard practice

The control pathway is standard practice for referral of patients with suspicion of retinal disease from community optometry to HES. Patients who attend a participating community optometry practice will undergo a clinical assessment and OCT scan. Patients with a suspicion of any retinal disease in the opinion of the community optometrist will be included in the study and will receive a referral decision (refer urgently to HES; refer routinely to HES; don’t refer to HES) by the community optometrist. All OCT scans and a clinical vignette from each case will be transferred to the Moorfields Reading Centre that will provide the reference standard for referral recommendations.

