#### Standard

OCT scans from the standard care and teleophthalmology arms will be transferred to the Moorfields Ophthalmic Reading Centre. The reference standard will be provided by the expert Ophthalmic Reading Centre for the C-RCT, diagnostic accuracy study and the pragmatic substudy. The reference standard will be the referral decisions and disease diagnosis made at the reading centre on the basis of review of images and clinical history and will apply to the RCT, the AI diagnostic accuracy study and the postimplementation, pragmatic substudy. Specifically, for each patient, the OCT scan (including b scans and colour fundus image) and a clinical vignette including visual acuity, age, symptoms, ocular and systemic history will be reviewed by two expert graders. The process to be followed is double grading with adjudication by a senior retinal specialist at the Moorfields Reading Centre.

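### Patients are enrolled after cluster allocation by an optometrist who knows the practice's arm, and the stated primary model cannot correct for differential recruitment

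*Protocol article*

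**What the plan says.** All places are in the protocol article.

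- **Allocation to trial groups.** "Optometry practices will be randomised 1:1 to standard care or teleophthalmology stratified by the hospital site", and "allocation concealment will be at the cluster level". Also: "Optometry practices are committed to the allocated study arm for the duration of the recruitment period", or until a minimum of 10 patients is reached. Patients therefore enter under an allocation already in force.
- **Participants.** "Only people with a suspicion of retinal disease in the opinion of the community optometrist will be recruited in the RCT and diagnostic accuracy study". Individual agreement follows: "patients who are approached and agree to take part in the study will consent" to data collection and analysis, with no randomisation of patients. Box 1 asks for any suspicion of a retinal condition and leaves exclusion for poor scan quality to the optometrist.
- **Control arm.** "Patients with a suspicion of any retinal disease in the opinion of the community optometrist will be included in the study and will receive" one of three referral decisions from that optometrist.
- **Intervention arm.** Hospital clinicians decide remotely. For the optometrist: "A referral recommendation by the community optometrist will also be recorded but not acted on".
- **Standard.** The reading centre sets the reference in both arms from the scan and vignette: "a clinical vignette including visual acuity, age, symptoms, ocular and systemic history will be reviewed by two expert graders", with a senior specialist adjudicating.
- **Statistical analysis.** The primary comparison is a logistic regression that accounts for clustered centres and reports adjusted odds ratios. The full analysis is left to online supplemental appendix 4, which is not shown.

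**The concern.** Randomising practices balances practices in expectation. It balances patients only if the same kind of patient is enrolled in both arms. Here enrolment comes after allocation and rests on a threshold that each optometrist sets. The article says nothing about masking, but the optometrist must know the arm: either their own referral stands, or the case goes through the platform to the hospital.

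The two arms also give different reasons to enrol. A control optometrist who has already decided not to refer may see little point in recruiting that patient. An intervention optometrist may send any doubtful case for a remote opinion, or may do the opposite. Any such difference changes the mix of patients on whom false positives are counted, and can create or hide a difference with no pathway effect at all.

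The intention-to-treat statement does not help, because no patient is randomised and the analysed set is formed after allocation.

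**Working it through.** **What can be reproduced.** The article states no sample size, expected false-positive rate or intracluster correlation, so there is no figure of its own to check on this point. The calculations below are illustrations on assumed inputs. Decision quality is identical in both arms, so the true odds ratio is 1. Odds ratios are teleophthalmology against standard care.

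**Which denominator.** The primary objective in Table 1 counts unnecessary cases among referrals. The Statistical analysis section speaks of a patient-level proportion without giving its denominator. Both readings are shown.

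**Illustration A: control practices enrol fewer of the patients they do not refer.** Assumed: prevalence 50%, sensitivity 0.90, specificity 0.50; the intervention arm enrols everyone. Per 100 eligible patients:

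- true positives 50 × 0.90 = 45, false negatives 5
- false positives 50 × 0.50 = 25, true negatives 25

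The control arm keeps all 70 referred patients and a fraction f of the 30 not referred.

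| f | False positives per patient | False positives among referrals |
|---|---|---|
| 1.0 | 25/100 = 25.0% | 25/70 = 35.7% |
| 0.7 | 25/(70 + 21) = 25/91 = 27.5% | 25/70 = 35.7% |
| 0.5 | 25/(70 + 15) = 25/85 = 29.4% | 25/70 = 35.7% |

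At f = 0.5 the spurious odds ratio per patient is (25/75)/(25/60) = 0.80. Among referrals it is 1.00 whatever f is, because f touches only patients who were not referred.

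**Illustration B: the arms differ in the share of reference-negative patients enrolled.** Write p for that share, with false-positive rate 0.5 among reference-negatives and sensitivity 0.9. False positives per patient = 0.5p. Among referrals = 0.5p / (0.5p + 0.9(1 − p)).

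| p, control | p, teleophthalmology | Per patient | OR | Among referrals | OR |
|---|---|---|---|---|---|
| 0.50 | 0.40 | 25.0% vs 20.0% | 0.75 | 35.7% vs 27.0% | 0.67 |
| 0.50 | 0.60 | 25.0% vs 30.0% | 1.29 | 35.7% vs 45.5% | 1.50 |

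With the false-positive rate varied from 0.3 to 0.7, the first row gives 0.72 to 0.77 per patient and the second 1.24 to 1.34; the odds ratios among referrals stay at 0.67 and 1.50.

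**Reading the two together.** The share among referrals is immune to pattern A but not to pattern B. The per-patient share is open to both. Accounting for practice or hospital site corrects the variance and removes differences between sites. It leaves a systematic difference between arms in who was enrolled, because arm and recruiter behaviour coincide at practice level.

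**The case against.** The strongest reply has four parts.

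1. **The model is not unadjusted.** A reader might infer that the primary analysis is unadjusted and does nothing about the problem. The article does not support that. It reports adjusted odds ratios that account for clustered centres and defers the rest to appendix 4. All that can be said is that the article names no patient-level covariate, which is common in a condensed article. This stands. It narrows the point about the model and leaves the design point intact, since a covariate list would not cure selection on an unmeasured threshold.
2. **Inclusion is written before the decision.** A reader might infer that patients can be enrolled once the decision is known. The control-arm sentence puts inclusion first, not referring is a listed decision, and referred and non-referred cases alike go into the diagnostic study. The case report form (appendix 5) is not shown. This stands in part: the sentence gives an intended order, but the article describes no step that fixes enrolment before the decision.
3. **The size can be overstated.** A reader might count false positives among reference-negatives. Illustration A then moves from 50% to 25/42.5 = 58.8% or 25/37.5 = 66.7%, a spurious benefit of about 9 to 17 points. No section gives that denominator for the primary outcome. On the objective's own denominator the same pattern gives no bias.
4. **Safeguards exist.** The reading centre grades both arms by the same process, and the optometrist's recommendation is recorded in the intervention arm as well. Both are real strengths. The first protects classification, not entry to the trial; the second supplies the data for a check.

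**Conclusion.** The point holds as a design weakness that should be addressed. Recruitment follows a known allocation, rests on the optometrist's opinion, and in the control arm is in the hands of the person whose decision is scored. The article describes no safeguard aimed at this, and accounting for clustering cannot provide one.

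The size and direction of any bias are unknown. On the assumed inputs, leaving out 30% to 50% of non-referred control patients shifts the per-patient rate by 2.5 to 4.4 points and the share among referrals by nothing. A 10-point difference in case mix shifts both measures, either way. That the optometrist knows the arm is inferred from the two pathways, not stated. Nothing in the article shows that such bias will occur, or that it would favour teleophthalmology.

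**What to change.** 1. **Order rule.** In both arms, record eligibility and consent with a time stamp before the optometrist's referral decision or recommendation is entered. This closes the route in illustration A where enrolment follows the decision. It does not stop an optometrist from anticipating the decision.
2. **Paired supportive analysis.** In the intervention arm, pre-specify a comparison of the optometrist's recorded recommendation with the remote hospital decision on the same patients, each against the reference standard. This is free of between-arm selection. State the caveat that a recommendation nobody acts on may differ from a standard-care decision.
3. **Diagnostics by arm.** Report the optometrists' own false-positive rate and the reference-standard case mix in each arm. Treat a difference as a warning, not as proof: behaviour may differ when the recommendation has no consequence, and 12 practices per arm can differ by chance.
4. **Partial adjustment.** Add age and visual acuity, already in the vignette, to the primary model or a sensitivity model, and say plainly that this does not remove selection on an unmeasured threshold. If appendix 4 already does so, a cross-reference is enough.

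The cost is a small order rule at the practice visit and a little more analysis. No new clinical measurement is needed.
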